
### **Study duration**

This is a five year study. The estimated time for enrolling all subjects through completing all follow ups is 42 months. Each subject's participation is eighteen months (12 months intervention, 6 months follow-up). The proposed project dates are September 2013 - September 2018.

### **Resources necessary for human research protection**

Describe research staff and justify that the staff are adequate in number and qualifications to conduct the research. Describe how you will ensure that all staff assisting with the research are adequately informed about the protocol and their research related duties. Please allow adequate time for the researchers to conduct and complete the research. Please confirm that there are adequate facilities for the research.


## Characteristics of the Study Population

### Target population

Study participants will be recruited by Penn Medicine (and LGH) or CVS Caremark on behalf of the health plans as a business associate. This study will recruit participants through employer partners of CVS Caremark who meet eligibility criteria including having diabetes and/or CVD as well as statin use with medication possession ratio 80%. We used CVS claims data starting 1/1/2010 to identify individuals likely to have diabetes (on the basis of diabetes medication use) and CVD (on the basis of a previously validated algorithm that is highly specific and that uses combinations of medications commonly prescribed to patients with CVD). The CVS database reveals that out of 2,030,494 overall statin users, a total of 179,963 are classified as having diabetes and an MPR for their statin of 80%, while 70,001 are classified as having CVD and a statin MPR80%. These individuals would therefore be potentially eligible for our study. The MPR was calculated over a 365 day period.

### Subjects enrolled by Penn Researchers

748

### Subjects enrolled by Collaborating Researchers

0

### Accrual

Potential CVS participants will be identified by reviewing CVS Caremark pharmacy claims records using our eligibility criteria of statin use and MPR80%. All potentially eligible employees within the CVS-covered group will be contacted via existing communication channels through CVS. Potentially eligible employees will have evidence of diabetes medication use and/or CVD medication use in the CVS pharmacy database. These individuals will be sent letters (paper or email) describing the study and inviting them to enroll. Participants will also be recruited from the University of Pennsylvania Health System or LGH. Potential participants will be identified by monitoring laboratory data, via weekly queries of the EPIC electronic medical record database. Primary care providers in the Penn Health System and LGH will be notified about the study and told that their eligible patients may be recruited. All eligible Penn Health System/LGH patients will be mailed letters by the study staff inviting them to sign up on the study website. Follow-up phone calls and emails will also be completed with these patients since contact information will be available through EPIC. If a participant has a direct/calculated LDL value meeting study inclusion criteria within the past 4 weeks, that value will be used as their baseline LDL and they will not need to complete the baseline lab test. Interested participants sign up for the study on line or by phone with a study coordinator based at UPENN and will be asked to provide informed consent. These individuals will have the option of entering data related to eligibility and their demographic and clinical characteristics through the Way to Health internet portal or by phone. Each potential participant will visit a local participating laboratory (either the Quest national chain of commercial laboratories or their doctor's office if they are from Penn Medicine/LGH) to confirm that their LDL is 100 mg/dl. The Quest corporation has 24 hour appointment scheduling and 2,000 lab locations; these locations are in every state as well as Puerto Rico. The enrollment interview and baseline labs will allow investigators to determine final eligibility for the study. Our group has agreements in place with the Quest chain allowing research participants nationwide to have phlebotomy (blood draws). In the context of generous participation incentives (as will be provided in this study), the requirement of providing biological specimens at local laboratories has not been a barrier to program implementation. In another ongoing study, we have used Quest to enable 500 participants to get labs drawn at local laboratories. Randomization will be performed through the Way to Health platform. Randomization will be stratified by employer (should more than one employer be involved to recruit a sufficient number of participants) and study device and will use block randomization with variable block sizes. After reviewing the intake data and LDL, research staff will notify each participant of assignment using their preferred means of communication. All participants will receive an electronic pill container through the mail and will receive careful instructions about study procedures for their assigned arm. Throughout the study, coordinators will remain available to answer questions about the device use and other study procedures. Power and Sample Size: A wealth of data from clinical trials of statin medications indicates that lowering LDL cholesterol by increments of even 10 mg/dl can lead to meaningful declines in CVD risk. A meta-analysis by the Cholesterol Treatment Trialists Collaboration

suggests that a reduction in 10 mg/dl in LDL potentially reduces CVD events by 5%. We present results from a two-step approach to the power calculation intended to detect differences of 10 mg/dl or greater between the control and each intervention arm, as well as a 5 to 10 mg/dl difference between the most and least effective intervention arms. Thus Step 1 compares each of the intervention arms versus control (3 comparisons); Step 2 compares each of the intervention arms to each other arm (3 additional comparisons). For these sample size estimates, we assumed a standard deviation of 28 mg/dl (based on a prior RCT). The nominal experiment-wise two-sided Type 1 error rate of 0.05 was maintained in step 1, by using a Bonferroni correction (i.e.,  $\alpha=0.017$ , derived as  $0.05/3$  for 3 comparisons) and in Step 2 by using Tukeys honest significant difference. Many possibilities exist for differences between the three interventions and control; the table below considers three possibilities for a sample size of 160 per group. For differences of 10 mg/dl or larger between intervention and control, simulation studies indicate at least 80% power to detect differences between all 3 interventions and control. For differences of at least 10 mg/dl between interventions, we have at least 90% power to detect at least one difference among arms; for differences of 5 mg/dl or larger we have 82% power to detect at least one difference among arms. To ensure our sample size of 160 for the 12 month endpoint, we assumed a dropout rate of 14.5 % and inflated the sample size to 187 in each arm ( $n=748$  in the entire study) . Sensitivity Analyses: Between November 2015 and July 2016 the device failed at rates that exceeded rates obtained in our earlier studies. We anticipated that this might increase the variance of the primary outcome, with some subjects perhaps responding positively with increased compliance to statin medication and some negatively with decreased compliance. Positive responses might reflect increased intervention from study staff, or the swapping out of one device for another spurring increased compliance. Negative responses might reflect frustration, particularly on the Process arm or the Process & Outcome arm, with the inconsistent devices. We note that our completion rates for lab visits are close to our expected rates of 85%, suggesting that the device issue has not had an impact on subject retention. APPROACH 1: As a sensitivity analysis, we increased our assumed variance by 7% (SD 29 versus SD of 28) and we decreased our effect size in the Process alone and the Process & Outcome arms by 10%. Given that only XX subjects were affected for over a month, we believe this to be a very conservative calculation of the negative impact of the device issue. Table 2 above shows that, while our power has declined somewhat, we still have close to 80% power or APPROACH 2: As a sensitivity analysis, we increased our assumed variance by 15% (SD 30 versus SD of 28). Given that only XX subjects were affected for over a month, we believe this to be a reasonable assumption. Our study was designed to detect differences of 10 mg/dl between control and treated group as this difference is deemed clinically relevant. Table 3 below shows there is some decline in power, but overall we retain good power to complete the study successfully under a number of scenarios.

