**Randomization.** Randomization will be performed through the Way to Health platform. Randomization will be stratified by employer (should more than one employer be involved to recruit a sufficient number of participants) and will use block randomization with variable block sizes. After reviewing the intake data and LDL, research staff will notify each participant of assignment using their preferred means of communication. All participants will receive an electronic pill container through the mail and will receive careful instructions about study procedures for their assigned arm. Throughout the study, coordinators will remain available to answer questions about the electronic pill container use and other study procedures.

**LDL Measurement Schedule.** Participants will have six LDL laboratory checks, at months 0, 3, 6, 9, 12 and 18 months. To maximize the likelihood that these LDL measurements are completed, the Way to Health participant tracking system will remind the study coordinators when each participant is due to visit a lab. We will obtain extensive contact information including preferred mode of communication - from each participant and update it at each follow-up visit. Participants who miss scheduled LDL checks will receive four reminders. Patients will receive \$50 after enrollment, initial blood work, and setting up the Glow Caps. A subset of participants will receive \$100 after enrollment to test whether higher participation incentives increase recruitment rate. Participants will receive \$50 for each subsequent lab check and \$75 for the 12 month LDL check (the primary outcome).

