### **Analysis Plan**

Data analysis plans. We will explore and describe participant attributes across the 4 arms using graphical approaches and summary statistics (means, medians, standard deviations and the interquartile range). The primary analysis will be intent-to-treat using a linear regression analysis of the effect of treatment assignment on the outcome of change in LDL from baseline to 12 months. The model will be stratified by center and baseline will also be added as a covariate in order to improve efficiency of the analysis. Secondary analyses will adjust for measures of socioeconomic status (SES) and educational attainment (EA). We will explore whether SES and EA act as effect modifiers. We will assess model fit using standard linear regression diagnostics. In additional exploratory analyses, longitudinal models will examine the series of LDL values over time, to determine the shape of the trajectory and consider whether those trajectories differ by treatment group. All hypothesis tests will be two-sided. As a secondary analysis, we will compare the effect of the interventions vs. control among the subgroup of patients who are African-American and/or Hispanic. To maximize the power for this exploratory analysis, we will pool participants in all three incentive arms and compare to control participants. Missing data: Given low rates of drop-out in our other financial incentive studies and because this trial is low-risk, we anticipate low rates of drop-out. As with our other studies, we are diligent in proactively encouraging complete follow-up. Generous participation incentives, as well as multiple reminders

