## 1 Descriptive Analyses

1. Baseline characteristics. (Table 1) Describe the two populations (Penn Medicine & Lancaster General) and the sample, stratified by arm (include numbers (%) missing for each variable)
  - a. Age
  - b. Sex
  - c. Race/ethnicity
  - d. Income/household size/financial situation/marital status
  - e. Education
  - f. Health condition
  - g. Patient Activation Measure (PAM)
2. LDL-c Descriptive statistics
  - a. Baseline LDL-c (mean, median, IQR, SD, 95% CI on mean)
  - b. Repeat for LDL-c and change from baseline,  $\Delta_{LDL}$ , at 3,6,9 months and 12 & 18 months in cross-sectional fashion
  - c. Determine rate of missing LDL-c by arm at 3,6,9 months and 12 & 18 months

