## 2 Inference

### 2.1 Primary outcome

- Linear regression model of primary outcome,  $\Delta_{LDL}$ , for month 12 of the study as a function of study arm with baseline LDL-c and population included in the model (Penn Medicine & Lancaster General)
- Primary analysis uses multiple imputation (MI) to adjust for missing data
  - Describe subjects who are missing 12-month LDL-c data (within 60-day window)
  - Imputation model: includes arm assignment, and all of the baseline covariates described above.

- Hypothesis testing as described in the protocol and in previous Habit Formation Trial. Use a family-wise type I error rate of 0.05.
  - Compare each arm to control using Holm-Bonferroni correction
  - Compare any arms that are significant (adjusted  $p < .05$ ) to each other using Tukey's Honest Significant Difference.

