### 3 Sensitivity analysis, Device Failure & Use of Multiple Devices

We will characterize our subjects' experience to explore possible impacts of the period with higher rates of device failure. Our study is not powered for hypothesis tests of these effects. These analyses will be exploratory. The following analyses will be conducted:

- a. Each subject will be coded 1/0 depending on whether their participation in the study involved a 'high device failure' period. For each stratum (and for each arm, we will create estimates and 95% CI of the mean LDL-C reduction by arm. We will estimate an alteration in effect size (difference in LDL-C reduction between arms) due to exposure to faulty devices.
- b. We will create a variable, quantifying the proportion of the intervention period in the window with properly functioning devices. For most subjects, this variable will be 1 (always functional;), but for subjects with say 2 months in the calendar window of faulty devices, this would be  $300/360=.83$ . We will compare the probability of completing the study (lab visit at 12 months) by whether the subject spent time in the window of a poorly functioning device.
- c. Lastly, we used 3 different devices in this study. Of interest is how the response to the intervention may have differed by device. This will be modeled and explored.

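### The protocol disagrees with itself on whether randomisation was stratified by pill-container device, and neither the primary nor the imputation model has a device or employer term; any cost is probably small and in the conservative direction.

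*Combined protocol and SAP*

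**What the plan says.** The protocol describes the randomisation four times. In Accrual: "Randomization will be stratified by employer (should more than one employer be involved to recruit a sufficient number of participants) and study device". In the Randomization paragraph of Design the same sentence reads "Randomization will be stratified by employer (should more than one employer be involved to recruit a sufficient number of participants) and will use", going straight on to the block method with no mention of device. Subject recruitment and Procedures repeat the Design wording. In all four places employer is a factor only if more than one employer takes part. The device-failure part of the protocol's Analysis Plan (item 4a) uses yet another description: it refers to subjects as having been randomised to a device.

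For the primary analysis, the protocol's Analysis Plan says "The model will be stratified by center and baseline will also be added as a covariate". SAP section 2.1 models 12-month LDL-c change "as a function of study arm with baseline LDL-c and population included in the model (Penn Medicine & Lancaster General". The same section gives the missing-data model: "Imputation model: includes arm assignment, and all of the baseline covariates described above". The covariates listed in SAP section 1 include neither device nor employer. That section names only two groups: "Describe the two populations (Penn Medicine & Lancaster General) and the sample, stratified by arm".

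Device type appears in the SAP only among the exploratory analyses of section 3: "Of interest is how the response to the intervention may have differed by device". No model is specified there.

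**The concern.** Blocks within device strata balance the arms on device, so between-device variation largely cancels out of the arm comparisons. A model without device still counts that variation as residual error. If device is related to the outcome, the reported standard errors are then larger than the true sampling variation, and the tests fall below their nominal level.

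As the plan stands, a reader cannot tell which factors the randomisation used, so cannot check the primary model against them. The one grouping factor in the model, health system, is not named as a stratification factor anywhere. At stake are a little precision in the three comparisons with control and a clear account of how the analysis follows the allocation.

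**Working it through.** **Inputs from the protocol (Accrual, power paragraphs).** Effect 10 mg/dl against control; SD 28 mg/dl; 160 evaluable per arm; two-sided per-comparison level 0.05/3 = 0.0167; dropout 14.5%; 187 per arm, 748 in total. SAP section 3 counts three devices.

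**Assumed.** R², the share of outcome variance explained by the strata after baseline and population, is not in the documents. I use 0 to 5% as the main range and 10% as an outer case. The SD of 28 is taken as the residual SD of the model without strata.

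**The plan's own figures.** SE of an arm difference = 28 × √(2/160) = 3.130 mg/dl. Power = Φ(10/3.130 − 2.394) = Φ(0.800) = 78.8% per comparison (79.0% at the rounded 0.017). That is within two points of the stated 80%, which came from simulations whose tables are not in the available text. 160/0.855 = 187.1, and 4 × 187 = 748.

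**Effect of leaving out the strata.** With allocation balanced within strata:
- true SE = 3.130 × √(1 − R²); model SE without strata = 3.130; overstatement = 1/√(1 − R²) − 1
- true level without strata = 2 × [1 − Φ(2.394/√(1 − R²))]
- power without strata = Φ(0.800/√(1 − R²))
- power with strata = Φ(3.194/√(1 − R²) − 2.394)
- gap between the highest and lowest of three equally sized, equally spaced device means = 28 × √(6R²)

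| R² | True SE | SE overstated | True level | Power without strata | Power with strata | Gain (points) | Device-mean gap (mg/dl) |
|---|---|---|---|---|---|---|---|
| 0 | 3.130 | 0% | 0.0167 | 78.8% | 78.8% | 0 | 0 |
| 0.01 | 3.115 | 0.5% | 0.0161 | 78.9% | 79.3% | 0.3 | 6.9 |
| 0.02 | 3.099 | 1.0% | 0.0156 | 79.1% | 79.8% | 0.7 | 9.7 |
| 0.05 | 3.051 | 2.6% | 0.0140 | 79.4% | 81.1% | 1.7 | 15.3 |
| 0.10 | 2.970 | 5.4% | 0.0116 | 80.1% | 83.5% | 3.4 | 21.7 |

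Gains are taken before rounding; at 5%, 0.8115 − 0.7942 = 0.0173.

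**The right comparator.** The gain must be read against the unadjusted analysis at the same R². Measuring from 78.8% throughout would give 81.1 − 78.8 = 2.3 points at 5%. That is too much, because balanced allocation on a prognostic stratum already reduces the true variance before any adjustment.

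**Simulation check.** 748 subjects, permuted blocks of 4 or 8 within three devices by two sites, 14.5% dropout, 4,000 runs per R². Without device in the model, the ratio of mean model SE to empirical SD was 1.00, 1.01, 1.02 and 1.03 at R² of 0, 0.01, 0.05 and 0.10. The two larger ratios fall below the formula's 1.026 and 1.054 because incomplete blocks and dropout loosen the balance. Simulated power without and with device was 79.4% and 81.0% at 0.05, and 80.1% and 83.5% at 0.10.

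**The case against.** The strongest reply is that this is an inconsistency of documentation plus an optional covariate. Device is named as a stratum in one of four descriptions. Employer is conditional everywhere, and the SAP names only two health-system groups, so there may be no employer factor to adjust for. The standard errors are too wide only if device predicts LDL change, and no section gives such an estimate. An R² of 5% needs a spread of 15.3 mg/dl between device means, more than the 10 mg/dl the plan treats as a clinically relevant intervention effect. Device also gets some attention already: the protocol's device-failure analyses add functioning-device time and a swap indicator to the primary regression, and SAP section 3 will explore response by device.

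Most of this stands, and it is why the point is stated conditionally. Two parts do not remove it. The exploratory analyses leave the primary model as it is, and functioning-device time and swaps arise after randomisation, so they cannot stand in for the stratum. Nor is an effect of device on the outcome far-fetched to the investigators: they allowed for device failures raising the SD to 29 or 30. If all of that extra variance lay between device strata, R² would be 1 − 28²/29² = 6.8% or 1 − 28²/30² = 12.9%. These are ceilings, because the protocol describes mixed positive and negative responses, and device terms capture only shifts in the mean.

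**Conclusion.** The point holds in a limited form. The four descriptions of the randomisation conflict over device, and neither the primary nor the imputation model includes a device or employer term. If device was a stratum and is prognostic after baseline and population, the standard error is overstated by up to 2.6% for R² up to 5%, and adjustment gains up to about 1.7 points of power. At 10% the figures are 5.4% and about 3.4 points. At R² of zero nothing changes. These sizes rest on the assumed R², an SD of 28, 160 per arm and near-complete balance within strata; the simulation suggests slightly less SE overstatement.

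A reader might go further in several ways that the documents do not support:
- That the analysis certainly departs from the randomisation and its error bars are certainly too wide. The strata are not settled, and the effect of device on LDL is not quantified.
- That device imbalance biases the estimates. If device was stratified, the blocks already limit imbalance; if it was not, the imbalance is a matter of chance. The tests remain valid either way.
- That the device stratum stands in for enrolment period. The protocol reports a failure window and swaps, but not which device was assigned at randomisation in which period.
- That employer-plan participants have no level in the model. The protocol allows them, but nothing shows that any enrolled.
- That the gap between 78.8% and the stated 80% makes this serious. It is small, and the plan's simulation tables cannot be checked.

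**What to change.** In the protocol, reconcile the randomisation text in Accrual with that in Design, Subject recruitment and Procedures. State the strata the randomisation system actually used, including whether health system was one.

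In SAP section 2.1, add those strata as fixed effects to both the primary and the imputation model, alongside baseline LDL-c and population. Code device as assigned at randomisation, never as after a swap. Include employer only if it was used, with a level for any employer-plan participants; if there were none, say so. If the record shows that device was not a stratum, correct Accrual; a device term is then optional.

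Enrolment is recorded as closed. If outcome data have already been seen, keep the stated primary model and report the strata-adjusted one as a labelled sensitivity analysis.

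The cost is a wording change and a few degrees of freedom (two for three devices, plus any employer levels) out of about 640, that is 4 × 160.

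### The stated power of at least 80% to detect all three interventions versus control is not reached at the 10 mg/dl design effect, and the 82% head-to-head figure does not cover a 5 mg/dl gap between best and worst arm

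*Combined protocol and SAP*

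**What the plan says.** The calculation is in the protocol, section Accrual, under Power and Sample Size. It has two steps. Step 1 compares each intervention with control (three comparisons): "The nominal experiment-wise two-sided Type 1 error rate of 0.05 was maintained in step 1" by Bonferroni, 0.05/3 for each comparison. Step 2 compares the interventions with one another, with error controlled "in Step 2 by using Tukeys honest significant difference". The inputs are an SD of 28 mg/dl and 160 analysed per arm, inflated to 187 for 14.5% dropout.

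Three power statements follow:

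- Step 1, differences of 10 mg/dl or more: "simulation studies indicate at least 80% power to detect differences between all 3 interventions and control".
- Step 2, differences of at least 10 mg/dl between interventions: at least 90% power for at least one difference.
- Step 2, smaller differences: "for differences of 5 mg/dl or larger we have 82% power to detect at least one difference among arms".

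The opening of the same paragraph sets the aim as differences of 10 mg/dl or more from control, "as well as a 5 to 10 mg/dl difference between the most and least effective intervention arms".

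Two device-failure scenarios come next. Approach 1 uses SD 29 with effects cut by 10% in the Process and the Process & Outcome arms, and says "while our power has declined somewhat, we still have close to 80% power". Approach 2 uses SD 30, repeats that the study was designed around 10 mg/dl, and concludes that power remains good.

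SAP section 2.1 changes the Step 1 test: "Compare each arm to control using Holm-Bonferroni correction". The SAP has no power statement.

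**The concern.** The Step 1 sentence refers to all three comparisons, while the Step 2 sentences refer to at least one difference, so the paragraph itself separates the two kinds of power. Rejecting all three nulls is harder than rejecting one. With these inputs even a single comparison falls just short of 80% at 10 mg/dl.

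In Step 2, the aim is a gap between the best and worst arm, while the 82% is attached to differences of 5 mg/dl without saying which arms are 5 apart. Read together, the two sentences suggest 82% power for a best-to-worst gap of 5 mg/dl.

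These figures bear on how null results are read. If one incentive arm misses significance, or process and outcome incentives do not separate, a reader who relies on 80% and 82% will take that as stronger evidence of no difference than the design can give.

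**Working it through.** **Inputs.** From the protocol, Accrual: n = 160 per arm, SD = 28, two-sided 0.05/3 = 0.0167 for each comparison with control, then Tukey among the three interventions. From SAP 2.1: Holm in place of Bonferroni. From the protocol's Design section: equal allocation.

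**One comparison with control at 10 mg/dl.**

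- SE = 28 × √(2/160) = 3.130
- 10 / 3.130 = 3.194
- critical value z(0.0167/2) = 2.394
- power = Φ(3.194 − 2.394) = Φ(0.80) = 78.8% (79.0% with alpha rounded to 0.017)

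This is the nearest match to the stated 80%.

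**All three comparisons.** If the comparisons were independent, all-three power would be 0.788³ = 48.9%. The shared control makes them positively correlated, so the joint power was simulated (four arms, pooled variance, 400,000 runs). Effects are mg/dl better than control.

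| Effects | All three, Bonferroni | All three, Holm |
|---|---|---|
| 10/10/10 | 59% | 75% |
| 10/10/20 | 67% | 81% |
| 10/15/20 | 78% | 89% |
| 10/20/20 | 79% | 89% |

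Under Bonferroni, all-three power cannot exceed the power of the weakest comparison. Any pattern with an arm at 10 is therefore capped at about 79%. With equal effects in every arm, all-three power reaches 80% at about 11.7 mg/dl (Bonferroni) or 10.5 mg/dl (Holm).

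**Step 2, Tukey among the three interventions, at least one difference.**

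| Effects | Best-to-worst gap | Power |
|---|---|---|
| 10/15/20 | 10 | 82% |
| 10/10/20 | 10 | 91% |
| 10/20/20 | 10 | 91% |
| 10/12.5/15 | 5 | 28% |
| 10/10/15 | 5 | 35% |

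The first row reproduces the stated 82%, and the next two reproduce the stated at least 90%. All three have extremes 10 mg/dl apart. With extremes 5 apart, power runs from 28% (middle arm halfway) to 35% (two arms equal).

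**Device-failure scenarios at the 10 mg/dl design effect.**

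- Approach 2, SD 30, every arm at 10: SE = 30 × √(2/160) = 3.354; 10/3.354 = 2.981; Φ(2.981 − 2.394) = 72% per comparison. All three: 50% (Bonferroni) or 67% (Holm).
- Approach 1, SD 29: the starting effects are in a table that is not in the text. Assuming 10 in every arm, the 10% cut gives 9/10/9. Power is then 65% to 75% per comparison, and 44% (Bonferroni) or 62% (Holm) for all three.

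**Sample size.** 160 / (1 − 0.145) = 187.1, so 187 per arm and 4 × 187 = 748 follow from the stated dropout.

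**The case against.** The strongest reply is that the protocol says many effect patterns are possible and tabulates three, and that those tables are not in the text. The pattern 10/10/10 cannot have produced the Step 2 figures, because Tukey would then reject only 5% of the time. The simulated patterns were probably unequal. For 10/15/20 the all-three power is 78% under Bonferroni, and under the SAP's Holm test 10/10/20, 10/15/20 and 10/20/20 all exceed 80%. This stands as far as it goes: 59% belongs to one pattern and one test. It does not rescue a general claim for 10 mg/dl or more, which fails at its lower limit under both tests when all arms sit there, and under Bonferroni whenever any arm does.

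A second reply is that the 82% is right. It is, if the sentence means arms 5 mg/dl apart. The conflict is only with the aim sentence, which measures the gap between best and worst.

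A third is that the Approach 1 figures depend on assumed effects. That also stands. Starting from 10/15/20 instead, and depending on which arms are cut, SD 29 gives all-three power of 79% to 86% under Holm and 64% to 74% under Bonferroni. For Approach 2, 10/15/20 at SD 30 gives 84% and 72%. The Approach 1 sentence also breaks off in the text, so its full claim is unknown.

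A fourth is that the primary model adjusts for baseline LDL, and the protocol does not say whether 28 is the SD before or after that adjustment. If it is before, and the residual SD were 26 (an assumption), 10/10/10 would give 83% under Holm but still only 69% under Bonferroni.

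A reader might infer from all this that the sample size calculation failed or that the trial has 59% power. The documents do not support that. Per-comparison power is within about 1 percentage point of 80%, the Step 2 figures reproduce, and the dropout inflation is right.

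**Conclusion.** The Step 1 statement is wrong as written. At 10 mg/dl, which the protocol names as its design effect, power is about 79% per comparison. All-three power is 59% (Bonferroni) or 75% (Holm) when every arm is at 10, so the chance of missing at least one effective arm is 41% or 25%. The 82% is correct for 5 mg/dl steps with a 10 mg/dl spread, and misleading beside an aim that starts at a 5 mg/dl spread, where the chance of finding no difference among the interventions is 65% to 72%.

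The fault lies in power and effect patterns that are not defined, together with one general sentence that its own inputs do not support. These results assume SD 28, 160 analysed per arm, a shared control and pooled variance. The patterns behind the stated figures are inferred from what reproduces them.

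**What to change.** Revise the Power and Sample Size text in the protocol's Accrual section and leave n unchanged:

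1. State Step 1 power at 10 mg/dl as about 79% per comparison, and give all-three power with every arm at 10 as 59% (Bonferroni) or 75% (the SAP's Holm procedure).
2. State that 82% assumes interventions in 5 mg/dl steps with a 10 mg/dl spread, and that power is 28% to 35% when best and worst differ by 5 mg/dl.
3. For the device-failure scenarios, also report power at the 10 mg/dl design effect. Approach 2: 72% per comparison, and 50% or 67% for all three. Approach 1: state the starting effects; if they were 10 in every arm, 65% to 75% per comparison, and 44% or 62% for all three.

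The cost is wording in the protocol only. No test, sample size or SAP text changes. The drawback is that the stated figures become less favourable.
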